#### Follow-up measures

At the 6-month follow-up (see below for follow-up procedures), the following measures will be recorded:

Point prevalence smoking abstinence: Self-reported smoking abstinence for 7-days before follow-up and exhaled air CO<10 ppm.^30^

Continuous abstinence: Self-reported smoking abstinence since end of treatment and exhaled air CO<10 ppm. Participants smoking five or fewer cigarettes during the 6-month follow-up will be considered self-reported quitters.^30^

Illicit drug use, collected at the end of the study from participants’ medical records.

All those lost to follow-up will be treated as smoking.^30^

#### Other measures

At the first stop smoking treatment session, a number of demographic and smoking behaviour variables will be recorded. The collection form for this information is shown in online supplementary appendix 2. As many contact details as possible will also be taken for the participants in order to increase the probability of participants being able to be followed-up. This will include the details of relevant friends and family members. Participants will also complete a satisfaction questionnaire on the last day of their participation in the trial, which will assess a number of satisfaction criteria including the value of incentives received (see online supplementary appendix 3).

### Follow-up procedures

Six months after their set quit date, participants will be contacted by the PI to ascertain their self-reported smoking status. The main purpose of this follow-up is to ascertain whether participants can be successfully followed-up for 6 months, and no group differences are expected to be found between the different conditions. To test the optimal follow-up method, participants will be pseudo-randomised by recruitment order to be contacted by text and phone call, or email and phone call. All participants will also be asked to return to the clinic in order to have their breath CO levels tested to verify abstinence. Once this is done, participants will have completed their participation in the study. Participants will receive a £10 voucher for completing the follow-up procedure.

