### Participants, recruitment, inclusion criteria and randomisation

As this is a pilot study, the primary outcome is not the efficacy of the study intervention. Consequently, the sample size has not been calculated to ascertain efficacy. Instead, the method outlined by Viechtbauer *et al*
24 for calculating the sample size based on the probability of any issues that may arise has been used. A sample size of 40 using the above rationale is powerful enough to provide over 90% certainty of detecting any issues that occur with a probability of over 5%.

The study therefore aims to recruit 40 patients, all undergoing current treatment for opioid addiction and who smoke ten or more cigarettes a day. Participants will be recruited from the study site, an outpatient drug addiction treatment centre, either through self-referrals in response to advertisements shown in the treatment centre or referrals from treatment centre staff. Participants are eligible for inclusion if they want to quit smoking (complete abstinence), are aged between 18 and 65 years, undergoing pharmacological treatment for opioid addiction, smoke a minimum of 10 cigarettes per day and provide informed consent. Use of smoking cessation medication is not a criterion for exclusion. Participants will be ineligible for inclusion in the study if they exhibit insufficient English skills to understand study protocols, are currently undergoing treatment for other drugs of abuse or if taking part in other research. Pregnant women will not be excluded.

Participants will be randomised into either experimental (CM for abstinence) or control (CM for attendance) conditions when recruited into the trial. Randomisation will be performed by the principal investigator (PI), using the service provided by the company ‘sealed envelope’,^25^ and will be performed using random permuted blocks within strata. Randomisation will be stratified based on participants’ current smoking frequency (between 10 and 20 per day, and more than 20 per day^6^). All participants will be given at least 24 hours after being given an information sheet to decide whether to take part, and will provide written consent, collected by the PI ([name]).

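### The protocol sets out to compare two follow-up contact methods but allocates them by recruitment order, which the PI can foresee; this weakens that comparison, with little effect on the smoking results

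*Protocol article*

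**What the plan says.** Under Follow-up procedures, the protocol article gives the 6-month contact a feasibility role: "The main purpose of this follow-up is to ascertain whether participants can be successfully followed-up for 6 months". It adds that no differences between conditions are expected at that point. It then builds in a second comparison, introduced by the words "To test the optimal follow-up method", and fixes how that comparison is allocated: "participants will be pseudo-randomised by recruitment order to be contacted by text and phone call, or email and phone call". The same section says that "participants will be contacted by the PI to ascertain their self-reported smoking status".

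Allocation to condition is handled differently. Under Participants, recruitment, inclusion criteria and randomisation, the PI collects written consent and randomises through an external service; this "will be performed using random permuted blocks within strata", the strata being two levels of daily smoking. Under CM intervention, the PI also administers the rewards and so knows each participant's condition.

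Under Follow-up measures, the rule for missing smoking status is "All those lost to follow-up will be treated as smoking".

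**The concern.** A comparison meant to choose a follow-up method for a later full-scale trial should not rest on a sequence that the enrolling person can read ahead. Here one person enrols, randomises, rewards and later makes the contacts, so each new participant's method can be known before that participant joins. The protocol does not say what recruitment order means in practice. If methods alternate, the sequence is predictable. If the first part of the sample gets one method and the rest the other, method is mixed up with calendar time and with anything that changes at the clinic meanwhile.

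Nothing in the text ties contact method to condition either, so the two can be unevenly crossed by chance. Because people not reached are scored as smoking, it is natural to ask whether that unevenness reaches the 6-month abstinence comparison. What is at stake is mainly how far the pilot's answer on contact method can be trusted, and secondarily some extra noise in a preliminary outcome.

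**Working it through.** The protocol gives no figure of its own for this comparison, so there is none to reproduce.

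**Inputs from the protocol article**
- Target sample of 40 ("The study therefore aims to recruit 40 patients"), taken as 20 per condition (1:1 is assumed).
- Condition allocated in permuted blocks within two smoking strata; block size not given.
- Contact method by recruitment order; rule not given.
- Lost to follow-up counts as smoking.

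**Assumptions**
- Contact methods alternate.
- Blocks of 2, 4, 6 or mixed sizes.
- 0%, 30% or 50% of participants in the second stratum.
- A gap in reach between the methods of 30 points (range 10-40).
- Abstinence of 10-30%.

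**Step 1: how uneven can method be across conditions?** Take ten blocks of 4 and ignore strata. Within a block, two places are text and two are email, and two of the four go to the experimental condition. The number of text places in that condition is 0, 1 or 2 with probability 1/6, 4/6 and 1/6, so the variance is 2 × 1/6 = 1/3. Over ten blocks the SD is √(10/3) = 1.83 around a mean of 10. The exact probability of a 13:7 split or worse, in either direction, is 0.166.

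Simulation over the block sizes and strata above (5,000 runs per setting) gives the difference between conditions in the share contacted by a given method:

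| Allocation of method | 20 points or more | 30 points or more |
|---|---|---|
| Alternation by recruitment order | 29-49% of trials | about 10-26% |
| Random, blocks of 4 within condition | none | none |

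A difference of 20 points is, for example, 12/20 v 8/20. For reference, a properly random 20/20 allocation that ignores condition gives 13:7 or worse in 11.3% of trials. Most of the imbalance therefore comes from not blocking within condition, and less of it from the sequence being non-random.

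**Step 2: what does an uneven split do to abstinence?** Shift in abstinence = (imbalance in method share) × (gap in reach) × (abstinence rate).
- Imbalance for 13:7 v 7:13: 13/20 − 7/20 = 0.30.
- Shift in follow-up: 0.30 × 0.30 = 0.09, or 9 points. With gaps of 10 and 40 points it is 3 and 12 points.
- Shift in abstinence with the 30-point gap: 0.09 × 0.10 = 0.9 points to 0.09 × 0.30 = 2.7 points.
- One participant in an arm of 20 is 1/20 = 5 points.

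**Step 3: does it change the behaviour of the smoking comparison?** This was simulated with 40 participants, condition in blocks of 4, 70% v 40% reached by the two methods, and no true difference between conditions.

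| Abstinence among those reached | SD of difference, alternation | SD of difference, blocked within condition |
|---|---|---|
| 30% | 11.9 points | 11.6 points |
| 20% | 10.0 points | 9.9 points |
| 10% | 7.2 points | 7.1 points |

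The type I error of the χ² test was 5.6% v 4.8%, 4.2% v 4.3% and 1.3% v 1.3% in the same order. The difference is practically nil.

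**Step 4: how much can the contact-method comparison show?** With about 20 v 20, power at two-sided 0.05 is about 25% for 50% v 70% reached, 51% for 50% v 80%, and 75% for 40% v 80% (reach rates assumed). It can only be descriptive, whatever the allocation.

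**The case against.** The strongest reply is that condition is randomised through an external service, so contact method behaves like any covariate fixed independently of condition. Imbalance has no preferred direction and the test's error rate already allows for it. That stands, and Step 3 bears it out. A reader might infer from the lost-counts-as-smoking rule that the scheme biases the 6-month smoking result; the documents do not support that.

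Several further points also stand.
- The 30-point gap in reach has no source in the protocol. Both methods include a phone call, and contact details of friends and relatives are gathered for everyone, which narrows any contrast.
- Alternation is an assumption, and the exact rule may be in the full protocol.
- The study is a pilot not sized for efficacy, and its primary outcome, completion of the 5 weeks, is not touched.
- The protocol is open that the method is only pseudo-randomised, and foreseeing text or email gives the PI no evident motive to alter anything.

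A reader might also infer that the follow-up rate will go unreported, since it is absent from the listed follow-up measures. That goes too far. The purpose is stated, the missing-data rule requires each person's follow-up status to be known, and an article commonly leaves the tabulation to the full protocol or analysis plan.

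The reply does not remove the core point. The allocation by recruitment order is stated, it is foreseeable by the person who fills every role, and a better tool is already in use in the same trial.

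**Conclusion.** The point holds as a minor weakness of the contact-method comparison. Its allocation is foreseeable, no balancing against condition is stated, and under a first-half/second-half reading it would be confounded with calendar time.

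Under assumed alternation, the conditions differ by 20 points or more in contact method in 29-49% of trials. The consequence for 6-month abstinence is chance noise of about 1-3 points in a 13:7 v 7:13 case, given an assumed 30-point gap in reach and 10-30% abstinence. That is not a bias. Changing the scheme is optional and should not be ranked with matters that affect the trial's main conclusions.

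**What to change.** Allocate contact method from a concealed sequence produced by the randomisation service already in use, in permuted blocks within each condition, and release each assignment only when that participant's follow-up falls due. Report the proportion reached by method and by condition descriptively. If methods have already been assigned, state the rule that was applied to recruitment order and give the same descriptive table.

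The cost is one extra allocation list and a sentence in the protocol, with no added visits or staff. The change removes foresight at enrolment and imbalance across conditions. It does not blind the PI to the method when making the contact, and it does not make a comparison of about 20 v 20 more than descriptive.

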### Planned analysis

As the primary objective of the intervention does not entail any hypothesis testing, the only statistics reported for this will be descriptive, namely means and SD for the number of participants retained at the end of treatment in each condition. Baseline demographics will be compared between conditions using t-tests for continuous and χ^2^ test for categorical data to ensure that any differences in these are not driving any potential differences in retention.

For the secondary objectives, differences between the groups in smoking cessation will be investigated using χ^2^ test, differences between conditions on opioid use and opioid treatment during the intervention will be compared using t-tests and χ^2^ tests dependent on data and any questionnaire data will be reported using descriptive statistics. All statistics will be performed as two-tailed tests using an alpha value of 0.05.

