### Objectives

Primary objective: To investigate whether a CM intervention can be successfully added to standard stop smoking services treatment, in patients undergoing outpatient treatment for opioid addiction, in order to identify any elements that need changing before carrying out a full-scale randomised controlled trial (RCT).

Secondary objective: To gather preliminary findings regarding the effects of the CM intervention on smoking in this group, and any possible effects the intervention may have on opioid addiction treatment outcomes.

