### Measures

#### Outcome measures

The primary outcome will be assessed by recording the number of participants completing the 5 weeks of the intervention in each condition. Success will be defined as 60% or more of participants completing treatment.

The secondary objectives of the study are to gather preliminary findings regarding the effects of the CM intervention on smoking in this group, and any possible effects the intervention may have on opioid addiction treatment outcomes. Smoking abstinence will be recorded as point prevalence and biochemically verified with abstinence defined as a breath CO reading of under 10 ppm^30^.Participants were informed that smoking cannabis would increase CO levels.

Participant medical records will be accessed after completion of the intervention to ascertain participants’ opioid addiction treatment, including treatment adherence, drug types (methadone, Subutex, so on), dosage and schedule (daily supervised pickup, weekly pickup, so on) as well as illicit drug use throughout the period of the trial.

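### The sample size and primary objective are about finding problems, but the only measure and statistic tied to that objective is a count of completers, which does not identify them

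*Protocol article*

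**What the plan says.** Four places in the protocol article bear on this.

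- **Objectives.** The primary objective asks whether the intervention can be added successfully to standard treatment, "in order to identify any elements that need changing before carrying out a full-scale randomised controlled trial (RCT"). No frequency of problems is named here.
- **Participants, recruitment, inclusion criteria and randomisation.** Efficacy is set aside as a basis for the sample size. Instead, a published method for "calculating the sample size based on the probability of any issues that may arise has been used". A sample of 40 is said to be "powerful enough to provide over 90% certainty of detecting any issues that occur with a probability of over 5" per cent.
- **Outcome measures**, and in the same sense the Abstract. "The primary outcome will be assessed by recording the number of participants completing the 5 weeks of the intervention in each condition". The criterion is: "Success will be defined as 60% or more of participants completing treatment".
- **Planned analysis.** For the primary objective, "the only statistics reported for this will be descriptive, namely means and SD for the number of participants retained at the end of treatment", by condition.

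The article does not define an issue, say where issues are recorded, or connect the 5% figure to completion.

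**The concern.** The sample size argument and the primary measure concern different quantities. The first is the probability that a given problem shows up in at least one of 40 people. It has meaning only if each participant is observed for that problem and the observation is kept. The second is the number who reach the end of five weeks.

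The section on the CM intervention describes a chain of steps at each session: a CO reading, a slip filled in by the cessation worker, hand-over to the principal investigator, a reward, and a reset where due. Any of these can go wrong without ending participation. The Discussion itself raises one such problem, that attendance-arm participants might think their reward depends on CO. A participant with that misunderstanding who keeps attending is simply a completer.

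At stake is whether the primary result answers the primary objective. As fixed, it will say whether at least 60% completed. It will not say which elements need changing, and the detection probability that justifies 40 participants has no recorded quantity behind it.

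**Working it through.** **Inputs.** n = 40, issue probability p = 5% and certainty over 90% (section on participants and recruitment); success at 60% completing (Outcome measures). The allocation ratio is not stated, so 20 per arm is an assumption.

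**1. The plan's own figure.** The chance of at least one occurrence among n participants is 1 − (1 − p)^n.

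- n = 40, p = 0.05: 1 − 0.95^40 = 1 − 0.1285 = 0.8715, or 87.1%. The stated figure of over 90% is not reproduced.
- Smallest p for which 40 participants give 90%: 1 − 0.1^(1/40) = 0.0559, about 5.6%.
- Smallest n for 90% at p = 0.05: ln(0.1)/ln(0.95) = 44.9, so 45 (1 − 0.95^45 = 90.06%; 44 gives 89.5%).
- One arm of 20: 1 − 0.95^20 = 0.6415, about 64%.

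**2. What the formula assumes.** It treats every occurrence as seen. If an occurrence is recorded only with probability s, the chance becomes 1 − (1 − ps)^n. With s = 1 this is the 87.1% above. For a problem that leaves the participant in the study, a completion count has s = 0, and the chance of detecting it by that measure is zero.

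**3. What the completion count can show.** A 5% problem is expected in 0.05 × 40 = 2 participants. Taking the 60% criterion over all 40, success needs 0.60 × 40 = 24 completers and so allows 40 − 24 = 16 non-completers.

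| Affected participant | Effect on the completion count | Problem identified? |
|---|---|---|
| Completes | None | No |
| Leaves because of the problem | One fewer completer | No; not distinguished from other non-completers |

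**4. What is collected elsewhere.**

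- Slips with CO for each session (CM intervention).
- NRT and e-cigarette use (Standard treatment).
- A satisfaction survey that includes the value of incentives (CM intervention; Other measures). Planned analysis handles questionnaire data with the secondary objectives.
- A test of whether six-month follow-up works, with two contact methods (Follow-up procedures).

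These bear on feasibility. None is named as a measure of the primary objective or of the 5% criterion.

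**The case against.** The strongest reply is that the trial as a whole is not blind to problems. The slips would reveal a missing CO reading, the survey asks about the incentives, and the follow-up is designed as a feasibility test. The Discussion already lists things to change, none of which comes from a completion count. This stands. A reader might infer that the trial cannot say what to change before a full-scale study, and the documents do not support that. The limit applies to the primary result.

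Secondly, the word *only* in Planned analysis comes after the remark that no hypothesis is tested. It can be read as contrasting descriptive with inferential statistics, and it does not forbid a narrative account of problems. That is fair. Even so, the sentence goes on to name retention as what will be described, and Outcome measures gives no other primary measure.

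Thirdly, an article condenses a fuller protocol, and an issue log may exist there. Its absence from the article is therefore not the point. The point is what the article does fix: one measure and one kind of statistic for an objective and a sample size that concern something else.

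Three other strong readings also fail:

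- The primary objective does not rest on a 5% rate. That figure belongs to the sample size text alone.
- It is not true that completion cannot register problems. Drop-out caused by a problem does enter the count, without its cause.
- One might argue that a 5% problem would move completion by only about 0.05 × 0.60 = 3 points, which is lost in the exact 95% interval of 43% to 75% at 24 of 40. The sizing method never proposes to detect issues through a shift in completion, so this comparison is not evidence against it.

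**Conclusion.** The mismatch is real, and worth correcting because the remedy is cheap. The sample size is justified by seeing an issue at least once and the objective is to identify what needs changing, while the only measure and statistic tied to that objective is the number completing five weeks. That number misses problems among completers and does not identify the problem among those who leave.

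The stated detection probability is also too high: 87.1% at p = 5%, with 90% reached only from about p = 5.6%. Within one arm it is about 64%, on the assumption of 1:1 allocation. All these figures assume that every occurrence is seen and recorded, and that occurrences are independent between participants.

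**What to change.** In Outcome measures and Planned analysis, add to the primary feasibility result a short, pre-listed tally per participant. The principal investigator would keep it from the slips and reward payments already handled. Suggested items:

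- slip or CO reading missing at an attended session;
- reward or reset misapplied against the plan's own schedule;
- participant dispute about, or misunderstanding of, the condition.

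For each item, report the number and proportion of all randomised participants with at least one occurrence, overall and by condition, with exact 95% intervals. Keep the 60% completion criterion. Reword Planned analysis so that retention is not the only primary statistic. Include reasons for non-attendance only where routine contact already supplies them, since a slip written after an attended session cannot.

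In the sample size text, state the probability for 40 participants as about 87% at p = 5%, with 90% reached only for p of about 5.6% or more. Give about 64% for one arm of 20 if allocation is 1:1.

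The cost is a little extra recording and one descriptive table. One weakness remains: the principal investigator pays the rewards and would be logging some of their own errors, so those items may be under-recorded.

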### Study design

A two-arm randomised controlled pilot study with 6-month follow-up. The intervention will be provided as an adjunct to the standard smoking cessation treatment provided at the treatment centre, with CM rewards available during 2–5 weeks of the smoking cessation treatment. The study will be conducted in compliance with the principles of the Declaration of Helsinki,^26^ the principles of Good Clinical Practice and all applicable regulatory requirements.

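### Baseline significance tests cannot show whether chance imbalance between the randomised arms explains a difference in retention

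*Protocol article*

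**What the plan says.** Planned analysis states that the primary objective involves no hypothesis testing and that retention in each condition will be summarised descriptively. It then adds between-condition tests of baseline demographics, t-tests for continuous variables and chi-square tests for categorical ones, and gives their purpose: "to ensure that any differences in these are not driving any potential differences in retention". All tests are two-tailed at 0.05.

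Study design describes "A two-arm randomised controlled pilot study with 6-month follow-up". The section on participants and randomisation says: "The study therefore aims to recruit 40 patients". It also says that "the sample size has not been calculated to ascertain efficacy". Allocation "will be performed using random permuted blocks within strata", and the only stratifying variable is smoking level: "Randomisation will be stratified based on participants’ current smoking frequency" (10 to 20, or more than 20, cigarettes a day).

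Outcome measures sets success at 60% or more of participants completing treatment and has completion recorded in each condition. The article gives no adjusted or stratified retention estimate. It also gives no rule for what follows a significant or a non-significant baseline test.

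**The concern.** The purpose clause asks the tests to settle whether baseline imbalance accounts for a difference in retention. That depends on two things: how large the imbalance is in the sample actually obtained, and how strongly the variable predicts retention. A baseline p-value mixes the first with the sample size and carries no information on the second. Its null hypothesis, that the arms are drawn from the same population, is already true if randomisation was carried out properly.

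The check can therefore mislead in both directions. A sizeable imbalance in a predictor of retention can pass as balanced. A significant difference in a variable unrelated to retention can cast needless doubt. This fault is one of principle and holds at any sample size; small arms make the false reassurance more likely.

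A retention difference between arms is a live possibility here, because the control condition rewards attendance itself while the experimental condition rewards abstinence. These tests are the only safeguard the article names for interpreting such a difference.

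**Working it through.** **Inputs.** From the protocol article: 40 participants, two arms, two-sided alpha 0.05, success threshold 60%. Assumed: 1:1 allocation, so n = 20 per arm; 5 to 15 baseline variables. The article refers to a number of variables and places the form in an appendix that is not shown.

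**The plan's own figure.** The article gives no figure for the behaviour of the baseline tests. The only figure attached to the sample size is the chance of seeing at least one occurrence of a problem. For a problem with probability 5% this is 1 − 0.95^40 = 0.871, against a stated certainty of more than 90% for problems above 5%. The 90% level is reached from 1 − 0.1^(1/40) = about 5.6%. That is a separate matter. Nothing below depends on it, and the rationale does not bear on comparisons between arms.

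**1. Smallest observed mean difference that is significant.** In SD units this is t(0.975, 38) × √(2/20) = 2.024 × 0.316 = 0.64. Any smaller observed imbalance is non-significant.

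**2. An observed imbalance of 0.5 SD.** t = 0.5/0.316 = 1.58 on 38 degrees of freedom, p about 0.12. It passes as balanced.

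**3. A categorical imbalance of 30 percentage points.** For 7/20 versus 13/20, chi-square = 40 × (7×7 − 13×13)² / 20⁴ = 40 × 14,400 / 160,000 = 3.6, p = 0.058 (0.11 with continuity correction). It also passes.

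**4. Could an imbalance that passes matter?** As an illustration, take an observed 0.6 SD (t = 0.6/0.316 = 1.90, below 2.024), retention of 60%, and an assumed correlation r of 0.3 to 0.5 between the variable and retention. The approximate shift in the retention difference is r × 0.6 × √(0.6 × 0.4):
- r = 0.3: 0.3 × 0.6 × 0.490 = 0.088
- r = 0.5: 0.5 × 0.6 × 0.490 = 0.147

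That is about 9 to 15 percentage points behind a non-significant test. With r = 0 the shift is nil however significant the test.

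**5. False alarms.** The chance of at least one p<0.05 in k independent tests under randomisation is 1 − 0.95^k:
- k = 5: 23%
- k = 10: 40%
- k = 15: 54%

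Correlation among the variables would lower these figures.

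**The case against.** The strongest reply is that little hangs on these tests. Retention is descriptive, the 60% rule has no between-arm component, the sample was not sized for efficacy, and no stated decision uses a baseline p-value. This stands, and it limits the consequence. A reader might infer that the retention comparison would be formally declared free of confounding, or that the trial's main conclusion is undermined. The article supports neither. No confirmatory test is invalidated, and the article states a purpose without a decision rule, so the step from non-significant to not driving retention is a natural reading of the clause and not a written rule.

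A reader might also describe the weakness through power, for example that a 0.5 SD difference is missed about two times in three with 20 per arm. That figure is power against a true population difference of 0.5 SD, and under randomisation there is none. What can affect retention is the observed imbalance, and at 20 per arm an observed 0.5 SD is non-significant every time. The 0.64 SD threshold is the relevant figure.

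The false-alarm rate rests on an unknown number of variables, and a list restricted to demographics may be short, so only a range can be given.

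Two further replies carry less weight. Baseline testing is common, but that does not make it fit for the stated purpose. It can have some use in checking whether randomisation was carried out properly, but the article does not give that reason. Lastly, the choice of an adjustment model is commonly left to an analysis plan that is not shown. That is fair, and the absence of a model is not the fault raised here. The fault is the purpose the article does state.

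**Conclusion.** The point holds in a limited form. The baseline t-tests and chi-square tests cannot establish whether imbalance drives a retention difference, whatever the sample size. With 20 per arm, imbalances up to about 0.64 SD, or 7/20 versus 13/20, would go unflagged. With 5 to 15 independent variables there is a 23% to 54% chance of at least one flag by chance alone. These figures rest on 1:1 allocation and on the assumed number and independence of the variables; the argument of principle needs only that participants were properly randomised. What is affected is the interpretation of a descriptive difference in retention between arms. The 60% success criterion is not affected.

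**What to change.** Delete the baseline tests and the clause giving their purpose, and tabulate baseline characteristics by arm without p-values.

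If a between-arm retention difference is reported or interpreted, give it as an exploratory estimate with a confidence interval, stratified by or adjusted for the randomisation stratum (10 to 20 versus more than 20 cigarettes a day), whatever imbalance is observed. A further covariate is optional and must be named in advance. Restraint is sensible: at 60% completion, 40 participants give 24 completers and 16 non-completers.

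The cost is a change of wording and, where a difference is reported, one extra estimate from data already collected. That estimate will be imprecise. With 60% retained in each arm of 20, the unadjusted 95% half-width is about 1.96 × √(2 × 0.6 × 0.4 / 20) = 0.30, or 30 percentage points. Showing that uncertainty tells the reader more than a set of baseline p-values.
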